### Training Plan

Training will be led by the principal investigator (a Namaste Care regional champion) with the support of community nurses [26]. Sessions will be delivered on weekends across 2 consecutive weeks, approximately 2 hours per day, supplemented by online modules to enhance access and optional individualized follow-ups for emerging challenges. The curriculum will cover the program’s history and core practices; practical use of the NCHP checklist and NCHP bag; assessment of pain, mood, and agitation; and illustrative activities (eg, memory books and dementia-friendly gardening). A concise NCHP manual will be provided before training and will be used as an ongoing reference. Following training, caregivers will apply skills at home with ongoing support, and a process evaluation 1 week after training will assess engagement and inform iterative updates to the manual and training [26].

### Stage 3: Execution and Evaluation Stage (Steps 9‐11)

#### Step 9: Test the Adapted Materials

We will recruit 4 people with dementia–caregiver dyads for a 2-week pilot to test the adapted NCHP in home settings [27]. After providing written informed consent, caregivers will implement the NCHP at home and use a daily checklist to record activities, task completion, and any tailoring (including adjustments to the NCHP bag as needs evolve). Upon completion, the principal investigator will conduct a focus group discussion with caregivers to collect feedback on feasibility, acceptability, and procedural clarity [28]; field notes will inform refinements prior to full implementation.

#### Step 10: Implement the NCHP

The adapted NCHP will then be implemented over 3 months in Lianyungang, with the research team providing ongoing supervision and responsive adjustments as needed. Baseline (T0) data will be collected using structured questionnaires before the intervention. For people with dementia, outcomes will include QoL and self-perceived burden; for caregivers, outcomes will include QoL, caregiver burden, caregiving capacity, attitudes toward dementia, and positive caregiving feelings. The purpose, instruments, and assessment schedule for both groups are specified in Tables1  2.

**Table 1. T1:** Data collection for people with dementia.

Data collected and tool used	Primary purpose	Time points of data collection		
		Baseline (T0)	Immediately after intervention (T1)	3-month follow-up (T2)
Sociodemographics	Age, gender, ethnicity, medical conditions, and access to social support such as family, friends, or formal care resources	✓	—^a^	—
QOL-AD^b^	Assess quality of life of people with dementia	✓	✓	✓
SPBS^c^	Assess the self-perceived burden of people with dementia	✓	✓	✓

a Not applicable.

b QOL-AD: Quality of Life-Alzheimer Disease scale; increased score reflects improved quality of life; the total score ranges from 13 to 52.

c SPBS: Self-Perceived Burden Scale; decreased scores reflect less perceived burden; total score ranges from 10 to 50.

**Table 2. T2:** Data collection time points for caregivers.

Data collected and tool used	Primary purpose	Time points of data collection		
		Baseline (T0)	Immediately after intervention (T1)	3-month follow-up (T2)
Sociodemographics	Age, gender, educational level, family structure (eg, relationship to the patient and presence of children or other dependents), living situation (eg, cohabiting with the patient, living alone, or in a care facility), and caregiving experience (eg, duration of caregiving)	✓	—^a^	—
WHOQOL-BREF^b^	Assess quality of life of caregivers	✓	✓	✓
C-ZBI^c^	Assess caregiver burden	✓	✓	✓
CTI-25^d^	Assess the caregiving capacity	✓	✓	✓
FAS-C^e^	Assess attitudes toward dementia	✓	✓	✓
C-PAC^f^	Assess positive feelings toward caregiving	✓	✓	✓

a Not applicable.

b WHOQOL-BREF: World Health Organization Quality of Life Scale- Brief Form Questionnaire; increased scores reflect improved quality of life; total score ranges from 0 to 100.

c C-ZBI: Zarit Burden Interview, Chinese version; decreased scores reflect less caregiver burden; total score ranges from 0 to 88.

d CTI-25: Caregiver Task Inventory-25; decreased scores reflect less complexity of caregiving tasks; total score ranges from 0 to 50.

e FAS-C: Family Attitude Scale, Chinese version; decreased scores reflect less adverse relational effects; total score ranges from 0 to 150.

f C-PAC: Positive Aspects of Caregiving Scale; increased scores reflect more positive caregiving emotions; the total score ranges from 0 to 55.

The NCHP coordinator will conduct regular check-ins with caregivers; during the first 2 weeks, reviews will be intensified to identify scheduling or checklist issues and enact immediate adjustments. Process evaluations will be conducted at weeks 2, 4, and 8 [29]. All protocol deviations (eg, withdrawal of consent and discontinuation) will be documented.

#### Step 11: Evaluate the NCHP

We will use a mixed methods approach that integrates quantitative and qualitative data to assess the feasibility, acceptability, and preliminary effects.

### Process 1: Data Collection

This feasibility study will use a 1-group pretest-posttest design. We acknowledge potential threats to internal validity (eg, history and regression to the mean), noting that this design is standard in feasibility research preceding more rigorous trials.

#### Feasibility Metrics

Feasibility benchmarks will be based on prior work [30] and will include the following: (1) NCHP application frequency (goal: ≥3 days per week, with ≥4 hours on at least 1 of those days); (2) retention over 3 months (goal: ≥75%, consistent with dementia-care feasibility studies [31]); and (3) incidence of AEs (goal: 0%; potential AEs include skin breakdown and falls). Although we aim for 0%, any AE will be closely monitored and addressed per protocol [32]. These thresholds will guide go, modify, or stop decisions for a subsequent trial: ≥75% for both retention and adherence=proceed; 60%‐74% for both=proceed with modifications; <60% for either metric=redesign, conditional on safety (no serious adverse events [SAEs] and all AEs appropriately managed).

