### Pilot Sample-Size Justification

This feasibility study prioritizes estimation precision over hypothesis testing. Therefore, we adopt a precision-based rationale for 10 to 15 dyads. For feasibility proportions (eg, 3-month retention and weekly adherence), a sample of 15 dyads yields an approximate 95% CI half-width of about +22 or –22 percentage points when the true rate is around 75% (and about +27 or –27 percentage points for n=10), which is sufficient to judge performance against feasibility thresholds. For continuous outcomes, a sample of 10 to 15 dyads provides approximately 24% to 19% relative precision for the SD (RSE(σ)≈√[1/(2(n−1))]), which is adequate to inform sample-size calculations for a subsequent trial. Regarding safety, if no adverse events (AEs) are observed, the “rule of three” places the upper 95% confidence bound on per-dyad AE risk at approximately 3/n (ie, no more than 20% for n=15), providing an acceptable early-phase safety screen. Taken together and consistent with previous feasibility studies of Namaste Care and related dementia interventions, a sample of 10 to 15 dyads is sufficient and appropriate to estimate key feasibility metrics and guide the design of a larger study.

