AEs include skin breakdown, falls, or activity-related discomfort, defined as any unfavorable and unintended sign, symptom, or event occurring during participation. SAEs are defined as events that result in death, life-threatening conditions, hospitalization or its prolongation, significant disability, or other medically significant conditions. Caregivers will be trained to recognize and document AEs and to report them immediately to the NCHP coordinator. The research team will assess severity and relatedness, determine whether an event is intervention-related, and take appropriate action. SAEs will be reported to the principal investigator and the ethics committee within 24 hours; nonserious AEs will be documented within 72 hours and summarized in periodic safety reports. Immediate first aid will be provided when necessary, and participants will be referred to community health services if required. If repeated or severe intervention-related AEs occur, the intervention may be paused, or the participant withdrawn; study-level suspension will be considered if predefined safety thresholds are exceeded. An independent safety officer will conduct an independent safety review at regular intervals to oversee AE logs and corrective actions.

Personal data collected during the trial will be handled and stored in accordance with applicable data protection laws, including the General Data Protection Regulation and the Personal Information Protection Law of China. Data will be pseudonymized upon study completion, and access to identifiable data will be restricted to authorized study personnel. All data and related documentation will be securely stored in compliance with regulatory requirements, and the use of study data will be controlled by the principal investigator.

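### The progression rule requires zero SAEs of any cause, so an unrelated death or hospitalization fails it; the relatedness assessment the protocol already makes is not used there

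*Protocol article*

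**What the plan says.** Under Feasibility Metrics, three tiers based on retention and adherence guide the decision about a later trial, and the decision is "conditional on safety (no serious adverse events [SAEs] and all AEs appropriately managed". No limit to related events is attached. The same section sets an AE goal of 0% and then qualifies it: "Although we aim for 0%, any AE will be closely monitored and addressed per protocol".

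Ethical Considerations supplies the definitions. An AE is "defined as any unfavorable and unintended sign, symptom, or event occurring during participation". For the serious category: "SAEs are defined as events that result in death, life-threatening conditions, hospitalization or its prolongation, significant disability, or other medically significant conditions". Neither definition mentions cause. The section then adds an attribution step: "The research team will assess severity and relatedness, determine whether an event is intervention-related, and take appropriate action". Attribution is used in the sentence on pausing the intervention or withdrawing a participant, which is confined to repeated or severe intervention-related events. An independent safety officer reviews the AE logs and corrective actions at intervals.

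According to Step 8 and the Results, all 15 dyads went on to the 3-month intervention. The people with dementia have a mean age of 83.5 years (SD 6.8); 10 are at the moderate stage and 5 at the late stage. Eligibility requires medical stability and living in the community.

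**The concern.** The progression condition should indicate whether the adapted program is safe enough to take into a larger trial. As worded, it counts every death, hospitalization or other serious outcome, whatever produced it. The cohort is old and has moderate or late dementia, so some such events may occur with no link to hand massage, games or aromatherapy. There is one group and no comparator, so the all-cause count cannot be set against an expected count. Attribution of individual events is the only means the protocol has of separating program from background, and the progression rule leaves it out.

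At stake is the main decision the study feeds. A program with 15 of 15 retained and full adherence would fail the safety condition after one unrelated admission. The team would then have to accept that outcome or override its own prespecified condition after seeing the data, and neither is a sound basis for a progression decision.

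**Working it through.** **The plan's own safety figure.** The Pilot Sample-Size Justification gives an upper 95% bound on per-dyad AE risk of about 3/n when no AEs occur. With n = 15, 3/15 = 20.0%. The exact one-sided bound is 1 − 0.05^(1/15) = 18.1%. The stated figure reproduces and is correct for the case it names.

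**Inputs.**
- Number at risk: 15 people with dementia (Step 8, Results).
- Condition: zero SAEs (Feasibility Metrics), all-cause by definition (Ethical Considerations).
- Background SAE risk p per person over 3 months: not in the document, so assumed and varied from 1% to 20%.
- Events independent between people, with a common risk: assumed.

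**Chance that the condition fails from background events alone.** P(at least one SAE) = 1 − (1 − p)^15.

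| Assumed 3-month risk p | (1 − p)^15 | P(at least one SAE in 15) |
|---|---|---|
| 1% | 0.860 | 14% |
| 2% | 0.739 | 26% |
| 3% | 0.633 | 37% |
| 5% | 0.463 | 54% |
| 10% | 0.206 | 79% |
| 20% | 0.035 | about 96% |

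**Break-even.** Setting 1 − (1 − p)^15 = 0.5 gives p = 1 − 0.5^(1/15) = 4.5% per 3 months. At a constant rate this is 1 − (1 − 0.0452)^4 = 17% a year.

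**The time window matters and is not fixed.** AEs are counted during participation, and assessments run to a follow-up 3 months after the intervention. If SAEs count over both quarters, the exponent is 30. The break-even falls to 1 − 0.5^(1/30) = 2.3% per 3 months, and 1 − (1 − p)^30 is 60% at p = 3% and 79% at p = 5%.

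**Whose events count matters too.** The definitions do not exclude caregivers (mean age 65.7 years). With assumed 3-month risks of 5% for people with dementia and 2% for caregivers, 1 − 0.95^15 × 0.98^15 = 66%, against 54% without caregivers.

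**Effect of using relatedness (illustration).** Suppose one SAE in ten were judged intervention-related. At a 5% all-cause risk, 1 − (1 − 0.005)^15 = 7%, against 54%. At 10%, 1 − (1 − 0.01)^15 = 14%, against 79%. The one-in-ten share is an assumption.

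**The case against.** Five points can be made for the plan as written.

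- **The failure probability depends on a rate the document does not give.** This stands. A reader might infer that the condition will probably fail in so old a cohort. The document does not show this: eligibility requires medical stability and community living, and for risks of 1% to 3% the chance over 3 months is 14% to 37%. Only the conditional statement with its break-even is supported.
- **The 0% AE goal does not block progression.** This also stands. A reader might take that goal as a second all-cause trip-wire. The section presents it as an aim, and the condition asks only that AEs be appropriately managed. A managed non-serious AE misses the goal and stops nothing.
- **The rule-of-three statement is sound.** It is explicitly limited to the case "if no adverse events (AEs) are observed". It makes no claim about one or more events, so it is not deficient.
- **An all-cause rule avoids a judgement.** Relatedness is assessed by an unblinded research team with an interest in the result, and the safety officer's stated task is to oversee logs and corrective actions, not to adjudicate cause. Changing the rule after enrolment also invites suspicion. These are real costs of the fix, but they can be limited by independent review of the classification, by showing all-cause counts alongside and by dating the change.
- **The thresholds only guide decisions, and fuller safety detail may exist elsewhere.** The article does not say which tier follows a failed safety condition, so some discretion remains. However, it states the rule and both definitions in full, and unseen detail does not change what they say together. Using discretion to set aside a stated condition after seeing the data weakens the prespecification.

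**Conclusion.** The point holds as a badly fixed decision rule. Combined with the all-cause definition under Ethical Considerations, the condition under Feasibility Metrics can fail because of background illness alone, whatever the program does, while the attribution step that could separate the two is used only for pausing or withdrawal.

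The size is conditional. For 15 people with dementia, independent events and a common risk, failure over 3 months is more likely than not once the background SAE risk exceeds about 4.5%, and that risk must be assumed. A longer window or the inclusion of caregivers lowers the break-even for people with dementia. The finding is confined to the SAE clause and should be corrected before results are interpreted.

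**What to change.** Reconcile Feasibility Metrics with Ethical Considerations as follows.

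1. Base the proceed, modify or redesign condition for the subsequent trial on SAEs judged intervention-related under the existing assessment.
2. Include that classification in the safety officer's existing log review.
3. State whose events count (people with dementia, caregivers or both) and over which window (to the end of the intervention or to the 3-month follow-up).
4. Report all-cause AE and SAE rates per dyad with exact confidence intervals beside the related counts, so that readers can see what the classification removed.
5. Date and document the change before results are interpreted, and say whether any SAE was known at that time.

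The reporting, management and pausing rules for participants stay unchanged; only the criterion for moving to a later trial is affected. The cost is a few sentences and a small addition to the officer's review. The downside to acknowledge is that relatedness is a judgement by an unblinded team and that the change comes after enrolment. Items 2, 4 and 5 limit that weakness but do not remove it.

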#### Qualitative Acceptability

Postintervention (T1) interviews will explore acceptability and caregiver experience, including perceived advantages and disadvantages, satisfaction with implementation, barriers and facilitators, and suggestions for improvement [33]. The interview guides are provided in Table S2 in Multimedia Appendix 2.

#### Quantitative Outcomes

Quantitative assessments will be conducted at baseline (T0), immediately after intervention (T1), and 3-month follow-up (T2). The primary outcome will be QoL, assessed using the Quality of Life-Alzheimer Disease scale for people with dementia (caregiver-report form; Cronbach α=0.87 [34]) and the World Health Organization Quality of Life Scale-Brief Form Questionnaire (WHOQOL-BREF) for caregivers (validated Chinese version; Cronbach α=0.70‐0.88 [35]). Secondary outcomes will include the Self-Perceived Burden Scale (Cronbach α=0.91 [36]) for people with dementia and the Positive Aspects of Caregiving Scale, Chinese version (Cronbach α=0.89 [37]), the Caregiver Task Inventory-25 (Cronbach α=0.93 [38]), the Zarit Burden Interview, Chinese version (Cronbach α=0.87 [39]), and the Family Attitude Scale, Chinese version (Cronbach α=0.93 [40]) for caregivers.

All measures have published psychometric support in Chinese samples; detailed properties and assessment schedules are shown in Tables1  2. Where available, instruments show acceptable test–retest reliability and sensitivity to change; where evidence is limited, we will prioritize feasibility signals and effect-size estimation to guide outcome selection for the subsequent trial.

### Process 2: Data Analysis

#### Quantitative Analysis

We will summarize demographics with descriptive statistics and analyze repeated measures using linear mixed-effects models at T0, T1, and T2 under a missing-at-random assumption for incomplete follow-up. Given the small pilot and feasibility focus, models will be parsimonious (time as a categorical fixed effect; random intercept only), estimated by restricted maximum likelihood with Satterthwaite small-sample degrees-of-freedom corrections in SPSS software (version 26; IBM Corp). We will report marginal means and effect sizes with 95% CIs, with primary emphasis on precision estimates; any *P* values will be descriptive. Diagnostics (eg, residuals) will be reviewed, with simple transformations or robust SEs applied if needed. Sensitivity analyses will use generalized estimating equations with small-sample-corrected robust SEs and complete-case paired summaries. We will also report variance components (random-intercept variance and intraclass correlation) to inform the design of subsequent, adequately powered trials.

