#### Step 8: Select and Train Caregivers

We will use criterion sampling [21] to recruit eligible dyads. Eligibility criteria for people with dementia include (1) age 60 years or older; (2) moderate-to-severe dementia as determined by the Mini-Mental State Examination [22], clinical symptoms, and caregiver report, confirmed by a trained evaluator; (3) medically stable; and (4) community-dwelling (noninstitutionalized). Caregiver eligibility criteria include (1) age 18 years or older; (2) provision of continuous, 24-hour in-home care for at least 3 months; and (3) ability to communicate effectively.

We will recruit a feasibility sample of 10 to 15 dyads to assess recruitment, retention, adherence, and acceptability rather than to test hypotheses [23]. Previous feasibility studies of Namaste Care and similar interventions have used comparable sample sizes [24], and Bowen et al [25] recommend using small sample sizes for exploratory feasibility objectives. Eighteen dyads were screened, and 3 were excluded, 4 dyads completed a 2-week pilot test, and all 15 dyads then proceeded to the 3-month intervention. (See Figure 4 for participant flow).

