## Results

Recruitment was conducted from January to April 2025 and yielded 15 caregiver–people with dementia dyads (n=30). Caregivers had a mean age of 65.7 (SD 11.7) years; 60% (9/15) were women, 66.7% (10/15) were married, and 73.3% (11/15) were retired or not working. People with dementia had a mean age of 83.5 (SD 6.8) years; 60% (9/15) were men, 66.7% (10/15) were in the moderate stage of dementia, 33.3% (5/15) were in the late stage, and 46.7% (7/15) were married, while 53.3% (8/15) were widowed. Recruitment is now closed, baseline assessments are complete, and data analysis is ongoing. Detailed participant characteristics are presented in Tables3  4.

**Table 3. T3:** Characteristics of caregivers (n=15).

Characteristics	Participants, n (%)	
Age (years)		
45‐59	4 (26.7)	
60‐74	6 (40)	
≥75	5 (33.3)	
Gender		
Men	6 (40)	
Women	9 (60)	
Nonbinary	0 (0)	
Marital status		
Married	10 (66.7)	
Widowed	2 (13.3)	
Divorced	3 (20)	
Employment status		
Working	4 (26.7)	
Not working or retired	11 (73.3)	

**Table 4. T4:** Characteristics of people with dementia (n=15).

Characteristics	Participants, n (%)	
Age (years)		
75‐79	4 (26.7)	
80‐84	6 (40)	
≥85	5 (33.3)	
Gender		
Men	9 (60)	
Women	6 (40)	
Nonbinary	0 (0)	
Marital status		
Married	7 (46.7)	
Widowed	8 (53.3)	
Stage of dementia category		
Moderate	10 (66.7)	
Late	5 (33.3)	

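### The planned sensitivity analyses cannot test whether loss that depends on unseen outcomes drives the preliminary QoL and burden estimates

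*Protocol article*

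**What the plan says.** The protocol article, under Quantitative Analysis, plans to "analyze repeated measures using linear mixed-effects models at T0, T1, and T2 under a missing-at-random assumption for incomplete follow-up". The model is deliberately small: "models will be parsimonious (time as a categorical fixed effect; random intercept only". It therefore holds no covariate that might explain who leaves. Two checks are named: "Sensitivity analyses will use generalized estimating equations with small-sample-corrected robust SEs and complete-case paired summaries". No weighting, imputation or departure from missing at random is mentioned, and inference is restrained: "any *P* values will be descriptive".

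Under Anticipated Challenges and Methodological Contingencies, attrition is listed as an expected risk. The same missing-at-random models and sensitivity analyses form part of the response. That section also promises to record why data are missing, but no stated analysis uses those reasons.

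On the population, "People with dementia had a mean age of 83.5 (SD 6.8) years", and 5 of 15 were in the late stage. Entry requires the person to be "community-dwelling (noninstitutionalized", but the article does not say whether a later move ends assessment. Death appears only in the definition of a serious adverse event. QOL-AD is completed by the caregiver.

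**The concern.** In a cohort this old and this advanced in disease, with caregivers providing round-the-clock care, some departures will plausibly follow a decline in the person or an overloaded caregiver. If that happens between visits, the value that explains the departure is never observed, and a model with only time and a random intercept cannot recover it.

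The named checks do not address this. Unweighted GEE generally needs data missing completely at random. A complete-case paired summary drops the partial records that help make missing at random plausible. If all three analyses agree, a reader may take the result as robust when they share the same blind spot.

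At stake are the preliminary effect sizes and variance components that the article intends to hand to a larger trial. If worse-off dyads leave, these would mostly describe the dyads that stayed.

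**Working it through.** **The plan's own figures.** The article gives no figure for missing outcome data. Its precision statements reproduce: 1.96 × √(0.75 × 0.25/15) = 0.219 and 1.96 × √(0.75 × 0.25/10) = 0.268 (stated as 22 and 27 points); √(1/(2 × 9)) = 23.6% and √(1/(2 × 14)) = 18.9% (stated as 24% and 19%).

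**How much loss the plan tolerates.** The retention goal is at least 75% over 3 months. With 15 dyads, 0.75 × 15 = 11.25, so 12 must stay and 3 may be lost (80% retained). T2 falls after that period, so loss by T2 may be greater.

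**Do the three analyses detect outcome-dependent loss?** A simulation of 400,000 subjects used these assumed inputs: intraclass correlation 0.6, total SD 1, true T0–T1 change 0.30, 20% lost after T0, and lower values of the driving variable more likely to be lost. The mixed model used the true variance components. Estimated change:

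| Loss depends on | Mixed model | Independence GEE | Paired complete-case |
|---|---|---|---|
| nothing (completely at random) | 0.30 | 0.30 | 0.30 |
| observed T0 value (at random) | 0.30 | 0.44 | 0.21 |
| stable latent level | 0.36 | 0.45 | 0.30 |
| unseen T1 value | 0.45 | 0.53 | 0.39 |
| unseen change | 0.45 | 0.39 | 0.49 |

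In the last two rows every estimate is too favourable, by 0.09 to 0.23. An exchangeable GEE with the same working correlation gives the mixed model's point estimates, so it would add no contrast on this question.

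**Illustration on the QOL-AD scale.** Assume stayers gain 1 point and lost dyads, all living, would have changed by d. The all-dyad mean is (number staying × 1 + number lost × d)/15.

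| d | 3 lost | 2 lost |
|---|---|---|
| 0 | 12/15 = +0.80 | 13/15 = +0.87 |
| −1 | 9/15 = +0.60 | 11/15 = +0.73 |
| −3 | 3/15 = +0.20 | 7/15 = +0.47 |
| −5 | −3/15 = −0.20 | 3/15 = +0.20 |

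The direction reverses at a decline of 12/3 = 4 points with 3 lost, and 13/2 = 6.5 points with 2 lost. A simulation of 300 replicates (15 dyads, one follow-up, between-dyad SD 4, within-dyad SD 2.5, lost dyads at −5) gave means of 0.91 (mixed model) and 0.94 (paired) with 3 lost, against the true −0.20. With 2 lost it gave 1.00 and 1.00, against +0.20. GEE was not run in this simulation.

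**Set against precision.** With within-dyad SD 2.5, the SD of change is √2 × 2.5 = 3.54. For 12 stayers the 95% half-width is 0.635 × 3.54 = 2.2 points. The gap of about 1.1 points (0.91 to −0.20) is half of that. In SD-of-change units, 3 of 15 lost shifts the mean by 0.20 for each 1 SD by which lost dyads differ from stayers, against a half-width of 0.64. With 6 of 15 lost the figures are 0.40 and 0.77.

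**The case against.** The other side has several good arguments.

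- A missing-at-random mixed model is a conventional primary analysis, and a statistical analysis plan not shown here may hold more detail. That stands: the primary model is no error, and silence on how death is handled is not itself the point. What remains is that the article does name a set of sensitivity analyses and presents them as part of its answer to attrition, and that set cannot probe the mechanism most worth worrying about.
- A reader might infer that the plan expressly treats death and care-home placement as missing at random. It does not. It speaks only of incomplete follow-up, does not mention later placement, and does not say that placement ends assessment. The fair statement is that reasons are not separated.
- A reader might infer that both checks rest on an equal or stronger assumption than the primary model, so that no analysis can reveal anything about departures. That fails for the paired summary. When loss depends on a dyad's stable level it gives 0.30, while the mixed model gives 0.36. The assumptions are not nested, and the paired summary is worth keeping.
- A reader might infer that all three analyses are always biased favourably when worse-off dyads leave. The simulation contradicts this. With loss driven by the T0 value, the mixed model is unbiased, independence GEE is too high and the paired summary too low. Such divergence would be informative.
- The stakes are modest. The article says "We will recruit a feasibility sample of 10 to 15 dyads to assess recruitment, retention, adherence, and acceptability rather than to test hypotheses", P values are descriptive, the emphasis is on intervals, and go/modify/stop does not use the QoL or burden models. This limits the weight of the point but does not remove it, because a wide interval does not correct a biased point estimate.

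**Conclusion.** The point holds in a limited form. One missing-at-random assumption covers all incomplete follow-up, and neither named sensitivity analysis can show dependence on the unseen outcome or change. Under such loss all three analyses can err favourably together (0.09 to 0.23 SD in the simulated cases, true change 0.30), so their agreement should not be read as robustness. These sizes rest on the assumed intraclass correlation, loss rate and dropout strength.

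The QOL-AD illustration rests on assumed changes of +1 for stayers and −5 for lost dyads, which have no source in the article. It shows that a sign change is possible at a loss the retention goal accepts. It does not show that one is likely: the shift lies well inside the interval, and both answers would read as no clear change.

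The consequence falls on the preliminary effect sizes and variance components carried forward. The effect on the variance components was not quantified here. The decision to proceed, modify or redesign is untouched.

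**What to change.** 1. Keep the mixed model, the GEE and the paired summaries. State that their agreement does not rule out loss related to unseen outcomes.
2. Report missingness at T1 and T2 by recorded reason. List deaths separately and impute no values after death.
3. Add one simple sensitivity analysis for QoL and burden. Set living dyads lost for health or caregiver-burden reasons to no change from baseline, then to a range of fixed worsening (for example 1, 3 and 5 QOL-AD points, with a comparable range for C-ZBI, where worsening is an increase). State the value at which the direction of change reverses. Because the values are fixed, read it as a test of the point estimate, not as a source of new intervals.

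This uses data already being recorded and needs a few lines of wording and code. The cost is slightly longer reporting and possibly a less favourable estimate.
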